## Abstract

**Background:**

The 2020 COVID-19 pandemic has witnessed wide-ranging efforts to minimize the spread of the virus and to protect those most vulnerable to becoming unwell following viral infection. Core COVID-19 preventive measures include social distancing, regular hand washing, and wearing face coverings in public places. Understanding links between social cognitive factors relating to beliefs/skills is important in the context of the COVID-19 pandemic, as this can suggest which factors might be targeted via behaviour change interventions to promote adherence to COVID-19 preventative behaviours. In this context, mental imagery exercises—self-directed imagining of an anticipated outcome or processes linked to a defined behaviour/activity—offer a well-evidenced, relatively simple behaviour change intervention. In the mental imagery invention reported in this protocol, individuals will be randomly assigned to one of four separate conditions (outcome imagery, process imagery, outcome and process imagery, control).

**Methods:**

The primary objective of this randomized controlled study is to assess the effectiveness of a mental imagery intervention on wearing face coverings, as a defined core COVID-19 preventative behaviour. Participants will consist of UK university students and university employees of any age. Participants will be randomized to complete an ‘outcome imagery’ or a ‘process imagery’ exercise, both exercises (i.e. a combined condition) or neither exercise (i.e. a control condition). A total of 260 individuals will be recruited into the study. Outcomes for all study condition arms will be assessed at baseline (Time 1), immediately post-intervention (Time 2), and at 1-month follow-up (Time 3).

The primary outcome is frequency of wearing face covering, as reported at T2 and T3. Secondary outcomes include intervention effects on face covering attitudes, social norms, perceived behavioural control and barrier self-efficacy at T2 and T3. Putative moderators of intervention effects are conscientiousness, narcissism and ‘light triad’ personality traits.

**Discussion:**

This trial will contribute toward the currently sparse evidence base concerning behaviour change techniques designed to promote COVID-19 preventative behaviours among UK university students and university employees.

**Trial registration:**

ClinicalTrials.gov (U.S. National Library of Medicine) NCT04583449. Retrospectively registered on 20 October 2020.

**Supplementary Information:**

The online version contains supplementary material available at 10.1186/s13063-021-05852-y.

## Administrative information

Note: the numbers in curly brackets in this protocol refer to SPIRIT checklist item numbers. The order of the items has been modified to group similar items (see http://www.equator-network.org/reporting-guidelines/spirit-2013-statement-defining-standard-protocol-items-for-clinical-trials/).

## Introduction

### Background and rationale {6a}

The 2020 COVID-19 pandemic has witnessed wide-ranging efforts to minimize the spread of the virus and to protect those most vulnerable to becoming unwell following viral infection. At the time of preparing this protocol, the three core ‘COVID-19 preventive measures’ included social distancing, regular hand washing and wearing face coverings enclosed public places [1]. Despite scientific debate around the evidence base in support of using face coverings in the context of the COVID-19 virus the scientific consensus overwhelmingly now supports the role of face coverings as a key protective measure pivotal to saving lives during the pandemic [2–4]. The current scientific consensus is that face coverings are an important mechanism for protecting others than face covering wearers themselves, and that even limited wearing of face coverings among the general public is likely to decrease viral transmissibility and, therefore, will save lives [5–7]. The UK government made using face coverings in defined indoor public areas (e.g. on public transport, in shops/supermarkets, in places of worship) a legal requirement in July 2020 and has been enforced with potentially substantial fines (up to £6400/$8700) [8].

Behavioural science has already guided understanding of how COVID-19 preventative measures, including face covering adherence, may be predicted. For example, evidence from varied continental settings has suggested that threat perceptions may predict adherence to COVID-19 preventive behaviours [9–12]. Given that face coverings primarily offer protection to individuals other than the wearer, individual threat perceptions and psychological theories concerned with risk susceptibility/vulnerability (e.g. Protection Motivation Theory; the Health Belief Model) may have less predictive utility in the context of the 2020 pandemic. Social-cognitive models have been tested to explain how variability in core beliefs relating to wearing face coverings might predict face covering adherence. For example, measuring whether individual’s hold (un)favourable beliefs about wearing face coverings (i.e. attitudes); perceived beliefs held by important others (e.g. friends and family) about wearing face coverings; or an individual’s perceived behavioural control or self-efficacy in the context of wearing face coverings [13, 14]. Various integrated social cognition models have been assessed as frameworks for predicting COVID-19 preventive behaviours [15–17]. For example, evidence has suggested that greater levels of preparedness to avoid foreseeable obstacles linked to a specific behaviour are predictive of increased COVID-19 preventative behaviour adherence at 1-week follow-up [15].

Understanding links between social cognitive factors relating to beliefs/skills is important in the context of the COVID-19 pandemic, as this can suggest which factors might be targeted via behaviour change interventions to promote adherence to COVID-19 preventative behaviours. At the time of writing few studies have tested interventions designed to elicit behavioural change in the context of COVID-19 preventative behaviours. Unpublished evidence revealed no difference in the impact of five health communication messages each of which emphasized a particular psychological mechanism involved in modifying the likelihood of adhering to COVID-19 preventative behaviours (e.g. self-protection, ‘sunk costs’, i.e. energies already invested in fighting the pandemic; disgust at non-adherent behaviour or easing cognitive load, i.e. message simplification) [18]. Given this paucity of empirical research exploring behaviour change interventions, despite the clear role for behavioural science in the context of COVID-19 preventative behaviour, it will be of interest to test the efficacy of a mental imagery behaviour change intervention. Mental imagery exercises are well evidenced, relatively simple behaviour change interventions in the context of behaviours relevant to promoting physical health and have been described by Conroy and Hagger as ‘self-directed imagining or visualizing specific events, actions or outcomes, including concomitant feelings and responses, with the express purpose of increasing motivation toward a target action or task’ (p. 669) [19]. Mental imagery interventions involve exercises requiring visualization and may also involve a written component relating to visualized health-related action. Mental imagery exercises can involve focusing on anticipated positive/beneficial outcomes of an action (outcome imagery) or imagery relating to the anticipated strategies/preparation that would be required to successfully execute a pre-defined action (process imagery).

While encouraging adherence to subsequent behaviour is the gold standard by which behaviour change interventions should be assessed, interventions can also be assessed in terms of their proven capacity to modify social cognitive ‘proxies’ of behaviour including those defined above (e.g. attitudes towards face coverings and skills involved in successfully wearing face coverings where required). In addition to belief/skill-based factors, variability in an individual’s adherence to wearing face coverings varies in association with what ‘type’ of person that individual is in dispositional terms will also be of interest. For example, a relatively conscientious person [20] might be expected to be more likely to routinely wear a face covering to protect nearby others from the risk of viral infection. Accordingly, personality traits relevant to COVID-19 preventative behaviours including ‘the light triad’ of Kantianism (i.e. treating people as valued in and of themselves), Humanism (i.e. valuing the dignity and worth of individuals) and Faith in humanity (i.e. beliefs that people are fundamentally good) [21] and conscientious, described above, are of interest. However, choosing to wear a face covering (or not) might vary in association with an individual’s vanity/egotistical self-image and therefore we will also assess whether/how intervention effects vary in association with narcissism [22]. Many mental imagery interventions employ measures of individual differences in dispositional skills or practice with using imagery relating to a defined behaviour [23]. Evidence has suggested that variability in skill/ability with visualizing (or, ‘imagery ability’) may modify the effectiveness of imagery intervention effectiveness (e.g. [24]). Imagery ability can, therefore, be a useful variable to gauge when testing imagery interventions.

This paper presents the study protocol for a three-part imagery intervention designed to encourage adherence to COVID-19 preventative behaviours. Participants are prompted to engage in the following three steps. In part 1, participants will be provided with information about the defined COVID-19 preventative target behaviour (i.e. wearing a face covering) as applied to a UK cultural context. In part 2, participants will be asked to visualize themselves wearing a face covering (the precise emphasis of this imagery exercise will vary depending on the study condition). In part 3, participants will be requested to record specific components derived from completing this imagery exercise (again, precise emphasis depending on condition) in written form.

### Objectives {7}

#### Goals and objectives

Drawing on recent meta-analytic conclusions which have substantiated the value of mental imagery interventions in the context of health behaviours [19] and a template approach for preparing rigorously developed, well designed mental imagery interventions [25], we planned to develop a theory-based behavioural intervention to promote face covering adherence, and more favourable social cognitions toward face covering adherence, among UK university employees and students. Individuals recruited will be randomly assigned to one of four separate conditions (outcome imagery, process imagery, both outcome and process imagery, control). Participants assigned to an imagery condition will be provided with information about the defined COVID-19 preventative target behaviour; will be asked to visualize themselves wearing a face covering; and will be requested to record specific features of imagery generated during the imagery exercise in written form. The control condition will receive a health warning message drawn from a pool of standard/representative UK government messages alone (representing a ‘usual care’ face covering warning control condition). Study measures will be taken at three time points: at baseline prior to randomization (i.e. Time 1, T1 hereafter); immediately post intervention (i.e. Time 2, T2 hereafter); and at 1-month follow-up (i.e. Time 3, T3 hereafter). The time interval between T1 and T2 will vary depending on intervention condition but will last approximately 15–20 min. The primary goal of this randomized controlled trial (RCT) is to evaluate the efficacy of a mental imagery intervention designed to promote face covering adherence on face covering behaviour at T3. The secondary goal of this RCT is to evaluate the efficacy of the imagery intervention on social cognitions at T2 and T3.

##### Specific objectives

To assess the impact of mental imagery interventions relative to a control condition comparing baseline measures (T1) with measures taken immediately post intervention (T2) and at 1-month follow-up (T3) relative to T1.To assess more favourable social cognitive indicators of face covering adherence at T2 relative to T1 and at T3 relative to T1.To assess relevant social cognitive factors (e.g. attitudes, normative beliefs, self-efficacy) as mediators of intervention effects on behaviour and cognitions at T2 and T3 (relative to T1).To examine personality traits as moderators of intervention effects at T3.To explore variability in imagery ability (how capable individuals are at visualizing future actions) as a moderator of intervention effects at T3.

##### Hypotheses

It is hypothesized that individuals assigned to any imagery intervention condition will report, at T2 and T3:

*H1*. Significantly higher levels of T2 behaviour (i.e. self-reported face covering adherence) relative to the control condition.

*H2*. Significantly higher intentions to wear face coverings in public places where these are required, relative to the control condition.

*H3*. Significantly more favourable attitudes, subjective norms, barrier self-efficacy and perceived behavioural control linked to face covering wearing relative to control condition participants.

*H4*. Finally, that imagery intervention effects will be conditional on being more conscientious, less narcissistic, and being characterized by higher levels of light triad personality traits.

### Trial design {8}

#### Methods/design

This study protocol is reported in accordance with Standard Protocol Items: Recommendations for Interventional Trials (SPIRIT) standard protocol items for clinical trials [26, 27]. For full details of the schedule of enrolment, interventions, and assessments for the planned intervention study, please consult Fig. 1.

**Fig. 1 Fig1:**
[figure not shown]
Schedule* of enrolment, interventions, and assessments for trial of mental imagery to improve adherence to face covering wearing adherence. *Adapted from SPIRIT Checklist guidance material displayed online under ‘Standard Protocol Items. Recommendations for Interventional Trials (SPIRIT)’. Self-reported face covering adherence for the previous week

#### Design

An experimental, prospective design will be adopted. Participants will be randomized to one of four conditions (outcome imagery; process imagery; outcome and process imagery; control ‘face covering warning’ condition). Mental imagery interventions will be evaluated against the control condition immediately post-intervention (T2) and at 1-week follow-up (T3). The evaluation will adopt a 2 (outcome imagery vs no outcome imagery) × 2 (process imagery vs no process imagery) × 3 (time: T1, T2, T3).

## Methods: Participants, interventions and outcomes

### Study setting {9}

#### Setting

This study will be conducted from two UK universities based in England. Given the social distancing restrictions following the COVID-19 pandemic, all measures will be gauged via Qualtrics, an online data collection interface (https://uelpsych.eu.qualtrics.com). There were divergences in the timing, duration, and stringency of their national responses by all four nations of the UK (England, Scotland, Wales and Northern Ireland) including formal evidence, for example, that Scotland took a relatively stringent approach to managing the pandemic relative to other UK nations [28]. Despite these differences, broad consistency in public health measures and economic support taken across UK nations has also been acknowledged [28]. Restricting focus to UK nations is important given that government guidelines and restrictions linked to the pandemic as well as the trajectory of the pandemic itself can diverge more considerably beyond UK nation strategic decisions. The UK has suffered relatively badly during the pandemic with, at the time of writing, over 8.2 million confirmed cases of COVID-19, over 550,000 COVID-19 related hospitalizations and over 137,000 deaths associated with COVID-19 recorded since 31st January 2020 [29–31]. Therefore, restricting the focus of the intervention reported in this article to the UK alone, as a national setting on which the impact of the pandemic has been relatively severe, is warranted.

#### Participants

A convenience sampling approach will involve recruiting adults aged 18 years or older who either study or work at one of two UK Higher Education institutions. Our eligibility/selection criteria will require participants to complete questionnaires at both time points; to be UK residents; to engage to a satisfactory level with intervention exercises; and to have regular exposure to circumstances/situations where wearing face coverings would be required under UK law. A focus on privileging the recruitment of individuals affiliated with university campuses (either as students or employees) is arguably justified given that (in circumstances of eased restrictions) travel to campuses, and social mixing in campus spaces would hold clear risks in terms of virus transmissibility. In reports of the intervention study, we will include details concerning the extent to which our final sample will be representative of the demographic characteristics found in the broader UK general population (e.g. in terms of age, sex, socioeconomic status). Full details of what study participation will involve in terms of activities and time requirements will be provided on the first page of the Qualtrics survey. Where individuals reading these details are willing to participate in the study, they will be able to provide their informed consent using a checkbox on the bottom of the first survey page.

### Eligibility criteria {10}

UK resident at time of completing questionnaires at all time points (T1, T2, T3)Completion of the full questionnaire at time pointsClear evidence of engagement with the mental imagery exercise (all responses will be screened and unclear/irrelevant or indifferent responses will be excluded from analysis).Regular (minimum of 2–3 times per week) exposure to indoor public places where face coverings would be required (under UK law)Provision of informed consent

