### Outcomes {12}

Study outcome measures are shown in Table 1. Behavioural outcome data will be recorded at T1 and T3 and psychological outcome data will be recorded at T1, T2 and T3 (see Fig. 1 for full details of the schedule of assessments). The primary outcome measure is self-reported face covering behaviour recorded at 1-month follow-up (i.e. T3). The secondary outcome measures include face covering intention, attitude, subjective norms, perceived behavioural control and barrier self-efficacy (T2, T3).

**Table 1 Tab1:** Study outcome measures^1^

Domain/construct	Tool^2^	Item(s)	Description
*Primary outcome*			
Behaviour^3^ (face covering adherence) recorded at T3 (i.e. 1-month follow-up)	Self-report measure using item adapted from Fisher et al. (2020)	1	Behavioural gauge of frequency of adherence to wearing face coverings where required.
*Secondary outcomes*			
Intention^4^	Self-report Likert measure items adapted from Theory of Planned Behavior Scale Construction Guidelines reported by Ajzen (2006)	3	Statement of an individual’s motivations/ plans to engage in the target behaviour.
Attitudes^4^		3	Statement of an individual’s beliefs/ endorsement of engaging in the target behaviour.
Subjective norms^4^		1	Statement of an individual’s perceived beliefs relating to important other peoples’ views about their engagement in the target behaviour.
Perceived behavioural control^4^		3	Statement of an individual’s perceived ability to successfully engage in the target behaviour.
Barrier self-efficacy^4^	Self-report measure using items adapted from Hamilton et al. (2019)	6	Statement of an individual’s perceived ability to successfully engage in the target behaviour when faced with obstacles.

^1^Please note that study outcomes are presented following the sequence in which they will be represented in the intervention study itself

^2^All constructs will be measured at T1 (baseline), T2 (immediately post intervention) and at T3 (1-month follow-up) except behaviour which will be measured at T1 and T3 only

^3^Timeframe = the previous week

^4^Timescale = the forthcoming week

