## Data collection and management

### Plans for assessment and collection of outcomes {18a}

#### Data collection and management

Participant names will not be included in the dataset and each participant will be assigned a study ID. All data will be downloaded in secure form to institutional cloud services (i.e. OneDrive). All data will be backed-up securely and all data files will be securely password protected and encrypted. Throughout project activities, data files and printed materials that are no longer required will be destroyed. Email address data will be stored in a separate document in an encrypted folder and will be destroyed once recruitment is completed. Range and consistency checks will be conducted on all questionnaire data promptly by the research team. Because questionnaire data will be collected using a ‘Force Response’ setting on Qualtrics there will be no missing data for this study. To address incomplete participant responses we will conduct an intention-to-treat (ITT) analysis in addition to the complete case analysis. ITT is an assessment of all trial participants in analysis regardless of whether or not they provided incomplete responses or failed to provide follow-up responses and provides a way of producing an unbiased estimate of intervention efficacy of the intervention in respect of study adherence [48].

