## Trial status

Enrolment for this study began on 19 August 2020 and ended on 28 February 2021. The total number of participants recruited includes a sample with complete data at T1/T2 only (*n* = 465) and a sample with complete data at T1 and T3 (*n* = 297). This study protocol is Version 2.0, dated 9 September 2020.

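### Eligibility depends partly on completion and UK residence after randomisation, which conflicts with the promised intention-to-treat analysis

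*Protocol article*

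**What the plan says.** The section Eligibility criteria {10} opens with "UK resident at time of completing questionnaires at all time points (T1, T2, T3". Its next criterion is completion of the full questionnaire, without naming the time points. The Participants section words it differently: "Our eligibility/selection criteria will require participants to complete questionnaires at both time points". The same eligibility list also has an engagement criterion, under which "all responses will be screened and unclear/irrelevant or indifferent responses will be excluded from analysis".

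The study has three assessments: "Study measures will be taken at three time points: at baseline prior to randomization", then T2 immediately after the intervention and T3 at one month. Sequence generation {16a} places the randomiser within the T1 survey, after the baseline measures.

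On outcomes, the protocol states: "The secondary outcome measures include face covering intention, attitude, subjective norms, perceived behavioural control and barrier self-efficacy (T2, T3"). The primary outcome, self-reported behaviour, is taken at T1 and T3 only.

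On analysis sets, Data collection and management plans an ITT analysis in addition to a complete-case analysis and explains that "ITT is an assessment of all trial participants in analysis regardless of whether or not they provided incomplete responses". It also says that forced responses will leave no missing data. Planned statistical analyses specifies ANCOVAs with T1, T2 and T3 as a within-participant factor.

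Trial status reports that the recruited total "includes a sample with complete data at T1/T2 only" (n = 465) and a sample with complete data at T1 and T3 (n = 297).

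**The concern.** An eligibility criterion should be decidable before allocation. Whether someone completes a later questionnaire, or is still UK-resident when answering T3, is known only afterwards. Applied literally, these criteria make a properly randomised person ineligible in retrospect, and the arms being compared are then no longer those that randomisation created.

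Return could plausibly differ by arm. Controls view a single image, the single exercises take about 8–12 minutes, and the combined exercise takes 15–25 minutes. The documents give no retention by arm, so neither the size nor the direction of any bias can be stated.

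Two sets of outcomes are exposed. The T2 secondary outcomes are recorded within the first sitting and need not depend on what happens a month later. The T3 primary outcome is exposed only for people who answer T3 after ceasing to be UK-resident.

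**Working it through.** **1. What can be known at allocation**

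| Criterion | Decidable before the T1 randomiser? |
|---|---|
| Consent, age, affiliation, exposure at T1 | Yes |
| UK residence at T1 | Yes |
| UK residence when completing T2 and T3 | No (T2 follows within minutes, so in practice T3 matters) |
| Questionnaire completion after T1 | No |

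**2. What each post-randomisation criterion can remove**

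- *Residence.* The list of three time points belongs to this criterion only, and it applies when a questionnaire is completed. Someone who never answers T3 does not breach it. It removes people who answer T3 while no longer UK-resident.
- *Completion.* No time points are named in the eligibility list, and the Participants section says both. If both means two sittings (T1 with T2, then T3), T3 is required and every non-returner is ineligible. If it means T1 and T2, non-returners stay eligible.

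**3. Set against the ITT statement**

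The ITT analysis is to keep participants who gave incomplete responses or no follow-up. The completion criterion makes complete responses a condition of eligibility. Either the ITT statement overrides the criterion, or the criterion leaves the ITT analysis with nobody extra to include. The protocol does not say which, nor whether ITT or complete case leads.

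**4. Size of the T2 loss if T3 is required**

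Inputs are 465 and 297, from Trial status. How the two samples overlap is not stated.

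- *The 297 are a subset of the 465:* 465 − 297 = 168 people without T3, and 168/465 = 36.1% of T2 records. With equal variance and an unchanged allocation split, the standard error ratio is √(465/297) = 1.25.
- *The samples are separate, and the 297 also have T2 data:* 465/(465 + 297) = 465/762 = 61.0%.

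Both figures count everyone without T3. A complete-case ANCOVA over T1, T2 and T3 drops the same people whatever the eligibility list says.

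**5. What that means for power**

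The plan's own figure comes first. For a fixed-effects ANCOVA, λ = N·f² and the denominator df = N − 4 groups − 6 covariates. With f = 0.25, alpha 0.01 and numerator df 3 (an assumption; the protocol does not state it), N = 254 gives λ = 254 × 0.0625 = 15.875, df = 244 and power 0.802. This reproduces the stated minimum of 254.

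With the same formula on the subset reading:

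| N analysed at T2 | Power at f = 0.25 | Detectable f at 80% power |
|---|---|---|
| 465 | 0.987 | 0.183 |
| 297 | 0.878 | 0.230 |

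**The case against.** The strongest reply is that the protocol never says T2 data will be discarded. It commits to an ITT analysis that keeps people without follow-up, and Trial status counts those with T1 and T2 data as recruited. Both suggest that these people remain in at least one analysis. This stands. A reader might infer that the eligibility rule as such throws away 36% of valid T2 data, but the documents do not support that. The loss depends on reading completion to include T3, or on running the three-time-point ANCOVA on complete cases, and the 36% is total T3 non-return.

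A reader might also infer that the eligibility list demands completion at T1, T2 and T3, and that it contradicts the Participants section. It does not say that: the three time points attach to residence. The word both can also be read as two sittings, which would reconcile the sections, although that reading still requires T3.

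Third, the consequences are limited. The T2 tests concern secondary outcomes. A non-returner's primary outcome is unobserved under any wording. Even 297 exceeds the required 254 and the target of 260. All of this is correct and lowers the severity.

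Fourth, Study setting {9} gives a reason for the UK focus: rules diverge more outside the UK. Answers from abroad may therefore reflect a different legal requirement, and keeping them in the main analysis is debatable.

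None of these replies makes a post-randomisation condition a valid eligibility criterion, or says how it sits with the ITT statement.

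**Conclusion.** The point holds as an unresolved conflict. Completion after T1 and UK residence at T2 and T3 are eligibility conditions judged after randomisation. Applied as written, they conflict with an ITT analysis of all participants whose rank against complete case is not stated.

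The possible cost to the T2 secondary outcomes is at most 36% of records (168 of 465), with standard errors about 1.25 times larger. This assumes that the 297 are a subset of the 465, and it reflects all T3 non-return. On the separate-samples reading the share is 61%. The effect on the primary outcome is confined to T3 responders no longer UK-resident, and the documents give no number for them. Bias by arm is plausible but cannot be quantified.

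This should be fixed. It does not show that the trial's results are invalid.

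**What to change.** 1. Limit eligibility in both sections to facts known before the randomiser: age, affiliation, UK residence and exposure at T1, and consent.
2. Treat later non-completion and non-residence as post-randomisation events to be reported by arm.
3. State that the ITT analysis leads and complete case is supportive.
4. Test T2 outcomes in everyone randomised with T2 data, and T3 outcomes in everyone randomised with T3 data, as allocated. Use a T1–T2 model for T2, or a mixed model over all time points, in place of a complete-case three-time-point ANCOVA. Changing the eligibility wording alone would not recover the T2 records. The mixed model's missing-at-random assumption for T3 should be stated.
5. Report T3 results with and without participants no longer UK-resident, given the stated reason for the UK focus.

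The cost is protocol wording and a change of model. Enrolment has closed, but no new data are needed, and the data-access section {31c} already foresees a protocol update after data collection. The remaining cost is that some T3 answers from outside the UK enter one of the two T3 analyses; their number and influence are unknown.
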